**4.3 Duration of Therapy**

In the absence of treatment delays due to adverse event(s), treatment may continue until one of the following criteria applies:

- Disease progression,
- Intercurrent illness that prevents further administration of treatment,
- Unacceptable adverse event(s)
- Patient decides to withdraw from the study
- General or specific changes in the patient’s condition render the patient unacceptable for further treatment in the judgment of the investigator.

**5. EXPECTED ADVERSE EVENTS / DOSE MODIFICATIONS**

**5.1**  **Expected Adverse Events Associated with BMS 247550**

The following adverse events have been associated with BMS 247550:

Common (>20% patients)

- Leukopenia / neutropenia (dose limiting)
- Thrombocytopenia
- Anemia
- Fatigue
- Alopecia
- Myalgia
- Arthralgia
- Sensory neuropathy
- Constipation

**Occasional (5-20% patients)**

- Nausea
- Vomiting
- Mucositis
- Rash
- Anorexia
- Diarrhea
- Insomnia
- Febrile neutropenia

Rare (<5% patients)

- Edema
- Allergy / hypersensitivity
- Muscle weakness
- Radiation recall phenomenon
- Tumor pain flare
- Pulmonary infiltrates/pneumonitis
- Taste disturbance
- Death

**5.2 Dosing Delays / Dose Modifications**

Prior to retreatment, patients must have recovered the following organ function:

- absolute neutrophil count 1.0 x 109/l
- platelets 100 x 109/l
- total bilirubin within normal institutional limits
- AST (SGOT) / ALT (SGPT) 2.5 x upper limit of normal
- creatinine 1.5 x upper limit of normal
- other Grade 0-1

Any patient experiencing the relevant toxicities (cited below in section 5.2) after one dose reduction will be removed from the protocol.

Patients should be dose reduced to 16 mg/m2 IV (20% dose reduction) over 1 hour in the event of any of the following:

- grade 4 neutropenia 5 days
- febrile neutropenia
- grade 4 thrombocytopenia
- grade 3 non-hematological toxicity
- 1 week delay for recovery from any toxicity

No patients should have his / her dose re-escalated following dose reduction.

**6. AGENT FORMULATION AND PROCUREMENT**

**6.1 Study Agent BMS 247550 (NSC #710428)**

**Chemical Name:** 1S-[1R*,3R*(E),7R*,10S*,11R*,12R*,16S*]]-7,11-Dihydroxy-8,8,10,12,16-pentamethyl-3-[1-methyl-2-(2-methyl-4-thiazolyl)ethenyl]-17-oxa-4-azabicyclo[14.1.0]heptadecane-5,9-dione.

**Other Names:**Epothilone B analog

**Molecular Formula:** C27H42N2O5S **M.W.:** 506.7 grams/mole

**Mode of Action:** BMS-247550 is a semi-synthetic analog of the natural product epothilone B. The epothilones are a novel class of non-taxane microtubule-stablizing agents obtained from the fermentation of cellulose degrading myxobacteria, *Sorangium cellulosum.*

**Description:**Epothilone B analog

**How Supplied**: BMS-247550 appears as a lyophilized, white to off-white color, whole or fragmented cake in a vial. The drug product is available in three different potencies: 15 mg/vial, 20 mg/vial, and 30 mg/vial.

Vial(s) containing Vehicle for Constitution of BMS-247550 for Injection, 8 mL/vial, 5.5 mL/vial, or 16.5 mL/vial are supplied with the lyophilized drug product The Vehicle for Constitution of BMS-247550 for injection (diluent) appears clear to slightly hazy and is colorless to pale in color. The diluent is comprised of an ethanol plus polyoxyethylated castor oil (Cremophor® EL) mixture (1:1 by volume).

One vial of the 8 mL/vial vehicle product is provided with the 15 mg/vial of BMS-247550 for Injection. Two vials of the 5.5 mL/vial vehicle product are provided with the 20 mg/vial of BMS-247550 for Injection. One vial of the 16.5 ml/vial vehicle product is provided with the 30 mg/vial of BMS-247550 for Injection.

The drug vial should only be reconstituted with the provided diluent. The diluents are not interchangeable and should only be utilized to reconstitute a particular strength.

Preparation: Prior to constitution of the lyophile, the diluent vial (s) should be kept at room temperature for approximately one hour. Inject 8 mL, 11 mL, and 16.5 mL of the diluent into the 15 mg vial, 20 mg vial, and 30 mg vial, respectively. Gently swirl the vial until the lyophile is completely dissolved. In all cases, this results in a 2mg/mL solution. The vial sizes and the required amount of diluent are summarized in the following table:

| BMS-247550 vial size | Diluent provided | Volume of diluent needed for reconsitution of drug vial | Final  concentration |
| --- | --- | --- | --- |
| 15 mg | One 8 mL vial | 8 mL | 2 mg/mL |
| 20 mg | Two 5.5 mL vials | 11 mL | 2 mg/mL |
| 30 mg | One 16.5 mL vial | 16.5 mL | 2 mg/mL |

This solution must be further diluted with Lactated Ringer’s Injection (LRI) to a final BMS-247550 concentration ranging from 0.1 mg/mL to 0.6 mg/mL in a non-PVC container before administration to the patient. Any remaining solution should be discarded according to institutional procedures for cytotoxics.

*Note:* 15 mg/vial potency: The label fill for the drug is 15 mg/vial which is to be constituted to a concentration of 2 mg/mL with the diluent. To account for vial/needle/syringe (VNS) loss, the actual amount of drug in the vial is 16 mg (+ 3%). Hence, the drug should be constituted using 8 ml of the vehicle for constitution (to achieve a BMS-247550 concentration of 2 mg/mL).

*Note:* 20 mg/vial potency: The label fill for the drug is 20 mg/vial which is to be constituted to a concentration of 2 mg/mL with the diluent. To account for vial/needle/syringe (VNS) loss, the actual amount of drug in the vial is 22 mg (+ 3%). Hence, the drug should be constituted using 11 mL of the vehicle for constitution (to achieve a BMS 247550 concentration of 2 mg/mL).

*Note:* 30 mg/vial potency: The label fill for the drug is 30 mg/vial which is to be constituted to a concentration of 2 mg/ml with the vehicle. To account for vial/needle/syringe (VNS) loss, the actual amount of drug in the vial is 33 mg (+ 3%). Hence, the drug should be constituted using 16.5 mL of the vehicle for constitution (to achieve a BMS-247550 concentration of 2 mg/mL).

**Storage**: BMS-247550 for Injection and the diluent for constitution should be stored refrigerated (2° to 8°C) prior to use and protected from light.

**Stability:** Shelf life surveillance is ongoing. After initial constitution with the accompanying diluent, the product may be stored for a maximum of 24 hours at room temperature and room light. After final dilution in Lactated Ringers for Injection (LRI) to concentrations between 0.1 and 0.39 mg/mL, the drug product is stable at room temperature and light for a maximum of 3 hours. When diluted with Lactated Ringers for Injection (LRI) to concentrations between 0.4 and 0.6 mg/mL, the drug product is stable at room temperature and light for a maximum of 6 hours.

CAUTION: The single-use lyophilized dosage form contains no antibacterial preservatives. Therefore, it is advised that the reconstituted product be discarded 8 hours after initial entry.

Route of Administration: The BMS-247550 infusion must be administered intravenously through an appropriate in-line filter with a microporous membrane of 0.22 to 5.0 microns. (See Incompatibilities section for a list of appropriate filters.) Lactated Ringers Injection (LRI) should be used to flush the IV line or extension set at the end of the infusion, if flushing is required.

**Reported Adverse Events and Potential Risks:**

Allergic reactions (anaphylaxis)/hypersensitivity (including drug fever), leukopenia, neutropenia, granulocytopenia, sinus bradycardia, edema, hypotension, fatigue (lethargy, malaise, asthenia), fever, alopecia, dermatitis, flushing, pruritus, radiation recall reaction, rash/desquamation, anorexia, constipation, diarrhea, nausea, stomatitis, dysgeusia, vomiting, febrile neutropenia, infection, muscle weakness (not due to neuropathy), dizziness/lightheadedness, insomnia, motor neuropathy, tingling, numbness, speech impairment (dysphasia or aphasia), syncope, arthralgia, myalgia, neuropathic pain, phantom limb pain, post-infection neuralgia, painful neuropathies, pain in extremities, cough, dyspnea, hiccoughs, hypoxia, pneumonitis/pulmonary infiltrates, urinary retention.

Also reported on BMS-247550 trials but with the relationship to BMS-247550 still undetermined: decreased hemoglobin, thrombocytopenia, hyperglycemia, hyperkalemia, hypocalcemia, transaminitis, ataxia, cerebrovascular ischemia (1 case), seizures (1 case).

**Potential Drug Interactions:** BMS-247550 may have a minimal potential to alter the metabolic clearance of drugs that are

highly metabolized by CYP3A4. When BMS-247550 was incubated with human liver microsomes along with compounds

specific for the inhibition of individual cytochromeP450s, significant inhibition was observed only with the CYP3A4 inhibitors

(troleandomycin and ketoconazole) suggesting that BMS-247550 may be a substrate for CYP3A4 in humans.

**Incompatibilities:** Contact of the diluted product with polyvinyl chloride (PVC) equipment or devices that are plasticized

with di- (2-ethylhexyl)pthalate (DEHP) should be avoided to prevent leaching of DHEP into the infusion medium. In order

to minimize patient exposure to DEHP, which my be leached from PVC infusion bags or sets diluted BMS-247550

solutions should preferably be stored in bottles (glass, polypropylene) or plastic bags (polypropylene, polyolefin) and

administered through polyetheylene-lined administration sets or PVC sets plasticized with TOTM (trioctyl trimellitate). IV

sets and components typically used for the administration of paclitaxel have been found to be compatible with infusions of

BMS-247550.

The following infusion components have been qualified for use with BMS-247550**:**

- IV sets containing an in-line 0.22 micron filter
  1. Baxter Vented Paclitaxel Set (Catalog #2C7553)
  2. Abbott Primary IV Plumset (Catalog #11947)
- IV sets not containing an in-line 0.22 micron filter (need to add one of the filters below)
  1. McGaw AccuPro Pump Nitroglycerin IV Set (Catalog #V8333)
  2. Clintec IV Fat Emulsion Set (Catalog #2C1105)
- Filter extension set (to be used with IV sets not containing an in-line filter)
  1. Braun Filter Extension Set with 5 Micron Filter (Catalog #FE-5010Y)

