1. OBJECTIVES

1.1 To assess the efficacy of BMS 247550 in stage IV malignant melanoma

1.2 To expand upon the known toxicity profile of BMS 247550 at the recommended phase II dose

1.3 To explore whether there is an association between pharmacokinetics at the recommended phase II doses with the extent of microtubule bundle and mitotic aster formation in peripheral blood mononuclear cells and tumor cells, where available. Total RNA, genomic DNA and total protein will also be extracted and stored from these cells for subsequent molecular analyses.

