**All patients will receive the following premedication to minimize nausea, vomiting and hypersensitivity reactions:**

**Diphenhydramine** 50mg IV (or equivalent,) 1 hour prior to BMS 247550

**Ranitidine** 50mg IV **(or equivalent)**, 1 hour prior to BMS 247550

**Ondansetron** 8mg IV/oral **(or equivalent)**, immediately prior to BMS 247550

**Dexamethasone** 20mg IV, immediately prior to BMS 247550

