**Patient Care Implications:**

Suggested Regimen for Treatment of Hypersensitivity Reactions

Primary prophylaxis (1 hour to 30 minutes prior to BMS247550):

- H1 blocker (diphenhydramine 50 mg po or IV)

H2 blocker (ranitidine 150 mg po or 50 mg IV or another equivalent H2 blocker)

Treatment and secondary prophylaxis:

- CTC Grade I Allergic/Hypersensitivity Reaction (transient rash, drug fever < 38°C): Supervise without further treatment.
- CTC Grade 2 Allergic/Hypersensitivity Reaction (urticaria, drug fever greater than or equal to 38°C and/or asymptomatic bronchospasm): Interrupt the infusion. If symptoms abate, attempt re-infusion at a slower rate. If the symptoms recur, discontinue infusion and follow guidelines below.
- Recurrent CTC Grade 2 or CTC Grade 3 or 4 Allergic/Hypersensitivity Reactions: Stop the infusion. Administer additional doses of H1 and H2 blockers intravenously. Administer IV steroids (see discussion below) and consider epinephrine and bronchlodilators as clinically indicated. Further treatment should be delayed 24 hours. Prior to rechallenge and with all subsequent cycles, give both an H1 and H2 blocker intravenously plus dexamethasone 20 mg x 2 doses (orally or intravenously) 12 and 6 hours pre BMS247550. Dexamethasone could be used at the investigator’s discretion in subsequent cycles for recurrent (i.e. occurring despite slowing infusion as discussed above) grade 2 reactions but would not be mandated.

Note that the administration of dexamethasone immediately prior to BMS247550 is unlikely to be effective.

**Note:** An extensive description of the expected adverse events associated with BMS 247550 is provided in Section 5.1 and Appendix A.

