**NYU 00-57 STUDY CALENDAR**

Baseline evaluations are to be conducted no more than 1 week prior to administration of study agent. Scans and x-rays must be done no more than 4 weeks prior to the start of therapy. If the patient’s condition is deteriorating, laboratory evaluations should be repeated no more than 48 hours prior to initiation of the next cycle of therapy.

|  | **Pre-Study** | **Each cycle** | | **Every 2 cycles** | **Off Study** |
| --- | --- | --- | --- | --- | --- |
| **D1, D8, D15** | **Prior to next cycle (D22-27)** |
| BMS 247550 |  | X |  |  |  |
| **Informed consent** | X |  |  |  |  |
| **Demographics** | X |  |  |  |  |
| **Medical history** | X |  | X |  |  |
| **Physical exam** | X |  | X |  |  |
| **Vital signs** | X | X |  |  |  |
| **Height / Weight** | X | X |  |  |  |
| **Medications** | X |  | X |  |  |
| **Performance status** | X |  | X |  | X |
| **Hb, ANC, plts*** | X | X | X |  |  |
| **Serum chemistry**** | X |  | X |  |  |
| **EKG (as indicated)** | X |  |  |  |  |
| **B-HCG** | X |  |  |  |  |
| **Adverse Events** |  | X | X |  | X |
| **Tumor Measurements** |  |  |  | X |  |
| **Collection of PBPC’s (1 & 24h: cycles 1 &2)** | X | X |  |  |  |
| **Tumor Biopsy (1 & 24h cycles 1 &2)** | X | X |  |  | X |

* If a patient develops Grade 4 neutropenia, CBC’s will be checked 3 times per week until resolution.

** Electrolytes, calcium, magnesium, liver function tests and LDH.

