**11.5 Reporting and Exclusions**

**11.5.1 Toxicity**

All patients will be evaluable for toxicity from the time of their first treatment with BMS 247550.

- - 1. **Evaluation of response**

All patients included in the study must be assessed for response to treatment, even if there are major protocol treatment deviations or if they are ineligible. Each patient will be assigned one of the following categories: 1) complete response, 2) partial response, 3) stable disease, 4) progressive disease, 5) early death from malignant disease, 6) early death from toxicity, 7) early death because of other cause, or 9) unknown (not assessable, insufficient data). [Note: By arbitrary convention, category 9 usually designates the “unknown” status of any type of data in a clinical database.]

All of the patients who met the eligibility criteria should be included in the main analysis of the response rate. Patients in response categories 4-9 should be considered as failing to respond to treatment (disease progression). Thus, an incorrect treatment schedule or drug administration does not result in exclusion from the analysis of the response rate. Precise definitions for categories 4-9 will be protocol specific.

All conclusions should be based on all eligible patients. Subanalyses may then be performed on the basis of a subset of patients, excluding those for whom major protocol deviations have been identified (e.g., early death due to other reasons, early discontinuation of treatment, major protocol violations, etc.). However, these subanalyses may not serve as the basis for drawing conclusions concerning treatment efficacy, and the reasons for excluding patients from the analysis should be clearly reported. The 95% confidence intervals should also be provided.

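### The chemistry footnote names no glucose, so asymptomatic hyperglycemia, an event the protocol lists as of unresolved relationship to the drug, is not systematically detected or graded

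*Protocol*

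**What the plan says.** Objective 1.2 is "To expand upon the known toxicity profile of BMS 247550 at the recommended phase II dose". Toxicity is a secondary endpoint (Section 11.1), and Section 11.5.1 states: "All patients will be evaluable for toxicity from the time of their first treatment with BMS 247550". Section 11.4 plans a description of related toxicities. Grading follows CTC version 2.0 (Section 10.2).

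Section 6.1, under reported adverse events, ends with events seen in BMS 247550 trials whose relationship to the drug is "still undetermined: decreased hemoglobin, thrombocytopenia, hyperglycemia, hyperkalemia, hypocalcemia, transaminitis". Ataxia, one case of cerebrovascular ischemia and one of seizures follow in the same sentence.

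The study calendar schedules serum chemistry at Pre-Study and once per cycle on days 22 to 27, before the next cycle. It schedules none on infusion days 1, 8 and 15. A footnote gives the content: "Electrolytes, calcium, magnesium, liver function tests and LDH".

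Section 4.1.1 introduces premedication with "All patients will receive the following premedication to minimize nausea, vomiting and hypersensitivity reactions" and includes dexamethasone "20mg IV, immediately prior to BMS 247550". The patient-care part of Section 6.1 is different. Its primary prophylaxis consists of an H1 and an H2 blocker. Dexamethasone enters only at rechallenge, and in later cycles it is discretionary for recurrent "grade 2 reactions but would not be mandated".

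**The concern.** Hyperglycemia is a raised blood glucose, so recognizing it without symptoms, and grading it, needs a glucose value. The protocol itself names the event as unresolved, yet its calendar schedules no such value before or during treatment. That corticosteroids can raise glucose is general pharmacology and is not stated in the protocol. If it is accepted, the premedication in Section 4.1.1 is a further reason to expect some raised values.

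Two things are at stake. First, a low count of hyperglycemia at the end of the trial could mean that it was rare or that nobody looked, and it would partly reflect which sites test glucose by habit. Data that were never collected cannot be recovered at analysis. Second, the protocol has rules that turn on grade. Section 5.2 ties dose modification to grade 3 non-hematological toxicity, and retreatment to other toxicity being grade 0-1. Section 10.2 ties expedited reporting to grade and expectedness. For an asymptomatic patient, these rules would rest on a value that no one is scheduled to obtain.

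**Working it through.** The protocol gives no figure to reproduce here. The check sets the events named in Section 6.1 against the tests in the study calendar.

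| Laboratory event of undetermined relationship (Section 6.1) | Scheduled test (study calendar) |
| --- | --- |
| Decreased hemoglobin | Hb |
| Thrombocytopenia | Platelets |
| Hyperkalemia | Electrolytes |
| Hypocalcemia | Calcium |
| Transaminitis | Liver function tests |
| Hyperglycemia | None named |

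Count: 6 laboratory events, 5 with a scheduled test, 6 − 5 = 1 without. No other section schedules glucose, so the number of scheduled glucose values is 0 per patient, at any sample size in the planned range of 23 to 88 (Section 11.3).

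**Steroid exposure under Section 4.1.1.** 3 infusions per cycle × 20 mg = 60 mg of dexamethasone per 28-day cycle.

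**Timing of the existing draw.** The last infusion of a cycle is on day 15 and chemistry is drawn on days 22 to 27. The interval is 22 − 15 = 7 days to 27 − 15 = 12 days. A glucose added to this draw would give a Pre-Study baseline and would show an elevation that persists. A brief rise in the days after dexamethasone could come and go before it.

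**Expectedness.** Hyperglycemia is in neither Section 5.1 nor Appendix A, the two places that Section 10.2 cites for expected events. It would therefore be handled as unexpected. Grade 2-3 with at least possible attribution calls for an expedited report within 10 working days, and grade 4-5 for a telephone report within 24 hours.

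**Other routes to detection.** The calendar collects adverse events on days 1, 8 and 15, before the next cycle and off study. Nothing prohibits an unscheduled glucose test. Symptomatic or incidentally measured hyperglycemia can therefore be recorded and graded. What is missing is systematic ascertainment of asymptomatic cases.

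**The case against.** The best counter-argument is that the footnote may be shorthand. It also omits creatinine, which Sections 3.1.7 and 5.2 require for eligibility and retreatment and which must therefore be measured. A site may run a standard panel that includes glucose. This lowers the certainty that glucose will go unmeasured, but it does not put a glucose test in the plan. Creatinine is at least demanded elsewhere in the protocol; glucose is not.

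A second objection is that no commitment is broken. Objective 1.2 does not promise a scheduled test for every term in a drug-information list, and the three neurological terms in the same sentence have no dedicated test either. That is fair, and it is why the point is minor. Those three would normally be recognized clinically, whereas a moderate glucose rise may not be.

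A third is that the remedy fits the steroid argument poorly: the existing draw falls 7 to 12 days after the last dexamethasone of the cycle, and a single arm cannot attribute a rise to drug or steroid. Both statements stand, and they limit what the added test can show. Baseline and persistent elevation remain worth having.

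On diabetes, Section 3 names no such exclusion, but Section 3.2.4 excludes uncontrolled intercurrent illness that would limit compliance, so poorly controlled disease is partly addressed.

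A reader might infer that the trial cannot detect or grade hyperglycemia, that it would report an incidence near zero, or that the toxicity objective fails as a whole. The documents support none of these. Adverse events are collected at every treatment visit, unscheduled tests are allowed, and one event term is affected.

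**Conclusion.** The point holds in limited form. Hyperglycemia is the only one of six laboratory events of undetermined relationship in Section 6.1 without a scheduled test. Asymptomatic cases are not systematically detected or graded, and there is no scheduled baseline.

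The number of cases that might be missed cannot be estimated, because the protocol gives no incidence; the firm figure is zero scheduled glucose values. The response endpoint, the stopping boundaries and the sample size are unaffected.

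The conclusion assumes that the calendar footnote is followed as written. It does not depend on how the dexamethasone conflict is settled, since it rests on Section 6.1 set against the calendar. Sections 4.1.1 and 6.1 do differ on whether dexamethasone belongs to primary prophylaxis, and Section 6.1 also doubts that giving it immediately before the drug is effective. Those passages must be reconciled.

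**What to change.** 1. Add glucose to the serum chemistry footnote of the study calendar, at Pre-Study and at the existing draw before the next cycle.
2. In Section 11.4, add a tabulation of CTC-graded hyperglycemia for all treated patients regardless of attribution. The present plan covers related toxicities, so events ascribed to the steroid could drop out.
3. State the limits beside the table: the day 22-27 draw addresses baseline and persistent elevation, may miss a transient rise after dexamethasone, and cannot separate the effects of BMS 247550 from those of dexamethasone in a single arm.
4. Reconcile Sections 4.1.1 and 6.1 on dexamethasone in primary prophylaxis. While the footnote is open, check whether its silence on creatinine is intended, given Sections 3.1.7 and 5.2.

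The cost is one analyte on blood already drawn and short edits to the calendar footnote and Section 11.4. The downside is a small laboratory expense and some asymptomatic values to report.
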